## Abstract

**Background:**

Reproductive and sexual health (RSH) concerns are common and distressing for young adults diagnosed with breast and gynecologic cancer and their partners. This study evaluates the efficacy of a virtual couple-based intervention called Opening the Conversation (OC). The OC intervention is grounded in theory and evidence-based practice and was adapted to improve coping and communication specifically in relation to RSH concerns after cancer.

**Methods:**

This Phase III trial is conducted in a fully remote setting and enrolls young adult couples (current age 18–44 years) with a history of breast or gynecologic cancer (stage 1–4, diagnosed under age 40) within the past 6 months to 5 years. Eligible dyads are recruited from across the USA. The target sample size is 100 couples. Dyads are randomly assigned to receive either the 5-session OC intervention or a 4-session active control intervention (Side by Side). The primary outcomes are change in reproductive distress and sexual distress. Secondary outcomes include communication about reproductive concerns, communication about sexual concerns, depressive symptoms, sexual function, relationship quality, relationship intimacy, sexual satisfaction, self-efficacy to communicate about sex and intimacy, and quality of life. An exploratory aim examines whether dyadic coping and communication quality mediate intervention effects on survivors’ and partners’ reproductive distress or sexual distress. Self-report outcome measures are assessed for both groups at baseline (T1), 2 weeks post-treatment (T2), and 3 months post-treatment (T3).

**Discussion:**

Despite the importance of RSH for quality of life for young adult cancer survivors and their partners, evidence-based interventions that help couples navigate RSH concerns are lacking. This randomized controlled trial will determine the efficacy of a novel couple-based intervention to reduce distress related to RSH concerns for younger couples after breast or gynecologic cancer, in comparison to an active control intervention.

**Trial registration:**

ClinicalTrials.gov NCT04806724. Registered on Mar 19, 2021.

**Supplementary Information:**

The online version contains supplementary material available at 10.1186/s13063-022-06665-3.

## Background and rationale

Breast and gynecologic cancers (BGC) are among the most common cancers in young adults [1]. Survival rates in this population are high, as are the long-term burden of cancer and its treatment on physical and psychosocial outcomes [2–4]. Young BGC survivors are at particular risk for reproductive and sexual distress due to exposure to gonadotoxic treatment and/or treatment affecting pelvic nerves and organ structures as well as scarring, loss of breasts or feeling in the breast, and pain [5–7]. The reproductive and sexual health (RSH) consequences of cancer, including worries about infertility, body image, dating and intimate relationships, and sexual function [7–12], are among the most common and distressing aspects of survivorship for young BGC survivors and their partners [13–19]. Indeed, whereas sexual changes are common and distressing for patients of all ages, younger survivors and couples are at even greater risk of psychological distress due to such changes compared to their older counterparts [20–22]. In sum, RSH concerns can negatively affect intimate relationships, family building plans, and quality of life well after treatment ends [6, 12, 13].

Despite how important intimate relationships and reproductive health are in the quality of life for young adult survivors [23], there are no evidence-based interventions in place to help young BGC couples struggling with distress surrounding both reproductive and sexual health concerns. Additionally, most couple-based interventions were developed for heterosexual couples and have not focused on meeting the needs of LGBTQ+ survivors and their partners [24]. This is important because LGBTQ+ couples tend to be less satisfied with the care they receive, may not feel welcome in clinical and support group settings, and are at heightened risk for significant unmet survivorship care needs, particularly related to psychological and sexual health [25–28]. Available approaches also often neglect the needs of partners. Finally, supportive care to help couples with RSH concerns is not widely available, particularly in rural areas, and barriers accessing such care remain high [29, 30]. When available, services typically rely on in-person formats for delivery and involve therapists with specialized training, who are often constrained to serving clients in urban centers and large cancer centers.

Research demonstrates that psychosocial interventions targeted at couples can enhance dyadic coping (i.e., coping together as a team) and communication in the context of cancer [24, 31–33]. These skills are critical for managing distress and maintaining relationship health and quality of life [34–37]. Specifically, couple communication about reproductive and sexual health is increasingly recognized as an important predictor of relationship functioning [38–40]. Both partners can experience fear, uncertainty, and relationship difficulties due to fertility concerns [41, 42], suggesting that addressing such concerns for both partners would be important in an intervention. Regarding sexual concerns, the most effective approaches to addressing sexual health and reducing sexual distress after cancer actively engage partners [43–45]. Couple-focused interventions, therefore, represent a promising approach to managing RSH distress after cancer.

Increasingly, psychosocial interventions for cancer survivors have been taking on a virtual format delivered via videoconference. Because virtual delivery of psychosocial interventions can remove barriers to access among those in less well-resourced cancer care settings and rural areas [46, 47], this format offers a promising approach to fill a gap in supportive care for young couples from all geographic areas faced with navigating life after cancer [9, 14]. Prior research points to the feasibility of a virtual intervention format [47], particularly for recruiting more ethnically and geographically diverse patients as well as less healthy patient populations [48]. The primary objective of this Phase III trial is to evaluate the efficacy of a virtual psychosocial intervention, Opening the Conversation (OC), to reduce RSH distress among young BGC survivors and their partners. OC was developed through systematically adapting an intervention initially designed to help couples cope with and communicate about cancer distress in general, called Side by Side (SS). OC was designed to help young couples cope together and communicate effectively about RSH concerns specifically. SS and OC are grounded in methods of cognitive behavioral therapy [34] and Bodenmann’s Systemic Transactional Model of dyadic coping [36, 49–53]. SS was previously modified from CanCOPE [54] in a pilot trial [55], then adapted specifically for virtual delivery with young adult BGC survivor couples in preparation for the current study [56]. In a prior in-person randomized controlled trial of SS, conducted in Germany with 72 heterosexual couples (female survivors of breast or gynecologic cancer and their partners, median age 52 years), couples receiving the SS intervention reported less avoidance in dealing with cancer, more posttraumatic growth, better communication quality, and better dyadic coping than those in an attention control condition [49]. A virtual version of SS, which focuses on general cancer-related distress, serves as the comparison condition to the OC intervention. The study conceptual framework is shown in Fig. 1. This manuscript describes the study protocol for a Phase III randomized controlled trial comparing two parallel conditions, OC and SS.

**Fig. 1 Fig1:**
[figure not shown]
Study conceptual framework

### Objectives

The specific aims of this study are:To evaluate whether the OC intervention leads to significantly greater improvement in reproductive distress and sexual distress reported by BGC survivors and their partners, as compared to the SS intervention (Aim 1a, primary outcomes)To evaluate whether the OC intervention leads to significantly great improvement in cancer survivors’ and their partners’ relationship (relationship quality, relationship intimacy, sexual function, sexual satisfaction, self-efficacy to communicate about sex and intimacy) and psychosocial health (depressive symptoms, quality of life) outcomes, as compared to the SS intervention (Aim 1a, secondary outcomes)In exploratory analyses, we will evaluate whether dyadic coping and communication quality mediate intervention effects on survivors’ and partners’ reproductive distress or sexual distress. (Aim 1b)

## Methods

### Trial design

The study will enroll 100 dyads (couples), each comprised of a breast or gynecological cancer survivor (diagnosed between 18 and 39 years of age) and their identified intimate/romantic partner. This is a two-group randomized controlled trial design with one pre-test and two post-test quantitative assessments. Dyads will be randomized to either OC or SS, with equal allocation to each condition. OC includes 5 weekly sessions, 90 min each. SS includes 4 weekly sessions, 90 min each. Both OC and SS are delivered remotely by a trained interventionist to participants across the USA. Web-based assessments are collected at baseline (T1), 2 weeks post-intervention (T2), and 3-month follow-up (T3). This study protocol has followed the Standard Protocol Items: Recommendations for Interventional Trials (SPIRIT) statement guidelines (See SPIRIT Checklist) [57]. The study will be conducted and reported according to the Consolidated Standards of Reporting Trials (CONSORT) criteria [58]. The study has been approved by the institutional review board (IRB) at Oregon State University (IRB 7621). The study flow is shown in Fig. 2.

**Fig. 2 Fig2:**
[figure not shown]
Study flow diagram

### Eligibility criteria

Cancer survivor participants are eligible if they meet the following criteria: (1) cancer diagnosis between the ages of 18 and 39, (2) current age 1844, (3) cancer diagnosis between 6 months and 5 years prior to enrollment date, (4) diagnosed with breast or gynecologic cancer, (5) self-reported cancer stages 1–4 at time of diagnosis, (6) self-reported ability to participate in a virtual intervention, (7) self-reported committed intimate partner who is willing to participate (any gender/sexual orientation), (8) English speaking, and (9) high-speed internet access via a smart phone, tablet, and/or computer.

Partners are eligible if they meet the following criteria: (1) age 18 or older, (2) English speaking, (3) self-reported ability to participate in a virtual intervention via videoconference, and (4) high-speed internet access via a smart phone, tablet, and/or computer.

Survivors and partners are excluded if either partner does not meet the eligibility criteria. Both partners must enroll in order to participate.

### Procedures

#### Recruitment and informed consent

Study recruitment is multi-pronged in that it includes a range of sources of participant identification, including study advertisements online via social media platforms, outreach through community partners, and letters mailed to potentially eligible cancer survivors in the Oregon State Cancer Registry (OSCaR). This strategy was selected both to facilitate achieving recruitment targets and to reach a diverse sample of dyads nationwide in light of the differences in survivors found through these sources.

Consent is obtained electronically after both partners complete screening procedures and potential participants can discuss their questions with a member of the research staff. Once both members of the dyad have completed consent, the dyad is considered to be consented. Enrollment is determined at randomization, after both partners complete the baseline assessment.

#### Data collection

Quantitative data are collected using Research Electronic Data Capture (REDCap). Each member of the dyad will complete separate surveys via REDCap at T1, T2, and T3, which are expected to take approximately 30 min each. Individual participants can receive compensation for the study of up to $30 in gift cards, or $60 in gift cards per dyad for completing all assessments. Strategies to increase retention include web-based surveys, flexible scheduling of intervention sessions, and sending email reminders. If either member of the dyad is unable or chooses not to continue participating in the intervention, both may be asked if they would be willing to remain in the study for data collection only and we will attempt to collect data as though they had participated in the assigned intervention.

Study staff complete training in human subject protection, secure data management, and protocols and procedures. All assessments occur in REDCap, which could reduce error related to manual data entry. Routine data checks are in place to check for data quality. Data safety and monitoring will occur in monthly investigator meetings. The group will monitor recruitment, enrollment, data collection, procedures, and any adverse events or protocol deviations (tracked and reported as required by the IRB). Data security is maintained through password-protected files, restricted access to datasets, and de-identification of data when possible.

#### Randomization

The study uses 1:1 blocked randomization (groups of 4), stratified by cancer type (breast versus gynecologic) and sexual orientation reported by the cancer survivor (heterosexual versus other). The study statistician generates the randomization sequence, and assignment to condition occurs via REDCap after the dyad has completed both the baseline assessment and videoconference orientation call with study staff. Couples are notified of their intervention assignment after scheduling their first session with the study interventionist. At that time, they receive both a mailed version and link to an electronic version of the participant materials. As with most behavioral interventions, the study interventionist, intervention supervisor, and participants are not masked to condition. However, although participants know whether they are receiving OC or SS, they are not told which of these is the experimental condition. The condition is masked to the PI, biostatistician, and research assistants who will evaluate quantitative outcome data. Quantitative outcome data is also collected via REDCap to minimize contact with participants while collecting study data. Should a review of adverse events reveal significant between-group differences that could warrant unmasking of the study conditions by the study biostatistician.

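### A single, published block size of 4 within four strata makes up to about a third of assignments deducible to anyone who knows the earlier ones; varying, undisclosed block sizes would be a cheap improvement

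*Protocol article*

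**What the plan says.** The Randomization section of the protocol article fixes the scheme: "The study uses 1:1 blocked randomization (groups of 4), stratified by cancer type" (breast or gynecologic) and by the survivor's sexual orientation (heterosexual or other). Two factors with two levels each give four strata. No other block size is mentioned.

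On who does what, the same section has the trial's statistician produce the list. On its use, the section says: "assignment to condition occurs via REDCap after the dyad has completed both the baseline assessment and videoconference orientation call with study staff". On masking, it says "the study interventionist, intervention supervisor, and participants are not masked to condition"; the PI, the biostatistician and the research assistants who evaluate the quantitative outcomes are masked. It states no masking for the staff who screen couples or hold the orientation call, and does not say whether they can see earlier assignments.

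The Trial design section sets the target at 100 dyads. The Trial status section says that recruitment opened in September 2021 and should run through 2023, so the block size became public while couples were still being enrolled.

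**The concern.** Concealing the list in REDCap stops people reading the next assignment. It does not stop them working it out. In a block of 4 with two couples per arm, the last assignment always follows from the first three, and the third follows from the first two whenever those went to the same arm. The strata offer little protection, because cancer type and orientation are reported by the survivor and known before assignment.

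The step just before assignment is a call that staff schedule and conduct. If a person involved in that step could predict the next arm, the timing of a call, or the effort spent on a hesitant couple, could drift with the expected arm without anyone intending it. That is selection bias. Masked outcome assessment would not offset it here, because the participants report the outcomes themselves and know which programme they receive.

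**Working it through.** The article gives no predictability figure, so there is none to reproduce. The check starts from the stated scheme.

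**Inputs from the protocol article.** Allocation 1:1, block size 4 and four strata (Randomization); 100 dyads (Trial design). The share of couples in each stratum is not given, so I tried four assumed mixes, from 25% in each stratum to 85/5/8/2%.

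**Assumed observer.** Knows the block size and every earlier assignment in the stratum.

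**1. Share of assignments that are certain, fixed blocks of 4.** There are 6 equally likely orderings of two couples per arm.
- Positions 1 and 2: never determined.
- Position 3: determined in 2 of 6 orderings, probability 1/3.
- Position 4: always determined, probability 1.
- Share = (0 + 0 + 1/3 + 1)/4 = **33.3%**.

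**2. Best-guess accuracy, fixed blocks of 4.** The best guess is the arm with fewer couples so far in the block. The chance of being right, by position, is 1/2, 2/3, 2/3 and 1.
- Mean = (1/2 + 2/3 + 2/3 + 1)/4 = 2.833/4 = **70.8%**, against 50% by chance.

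**3. Allowance for unfinished blocks.** In a simulation of 100 dyads over four strata, the certain share is about **31.7%** in all four mixes, or about 32 of 100 dyads. The assumed mix hardly matters.

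**4. The alternative: sizes 4, 6 and 8, equally likely, sizes hidden, block starts known to the observer.** This observer must always allow that the current block has size 8. An assignment is certain only when one arm has already received 4 couples, which can happen only in a block of 8.
- Expected certain assignments in a block of 8: 20% × 8 = 1.6.
- Expected certain assignments in blocks of 4 and 6: 0.
- Share = 1.6/(4 + 6 + 8) = 1.6/18 = **8.9%**.
- Simulated over 100 dyads with unfinished blocks: about 7.5 to 7.7%.

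**5. Best-guess accuracy under the alternative.** Guessing the arm with fewer couples so far needs no knowledge of the size. Expected correct guesses per block are 2.833 (size 4), 4.100 (size 6) and 5.329 (size 8).
- Mean = (2.833 + 4.100 + 5.329)/18 = 12.262/18 = **68.1%**.

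| Scheme | Certain | Best guess right |
|---|---|---|
| Fixed 4 (as planned) | 33.3% | 70.8% |
| Random 4/6/8, sizes hidden, starts known | 8.9% | 68.1% |

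For comparison, mixing only 4 and 6 on the same terms leaves about 14% certain in the simulation of 100 dyads, so including size 8 is worthwhile.

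**The case against.** The strongest reply is that the article shows no route for the leak. Exploiting the blocks needs one person, or a connected group, who both tracks assignments by stratum and influences which couple enters next. The only staff named as unmasked are the interventionist and the supervisor. The article gives them training, delivery and supervision, not screening, consent or orientation calls. The statistician makes the sequence and REDCap issues it after baseline. Staff access rules are also a detail that a condensed article may leave to the full protocol.

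Most of this stands, and it makes the one-third figure an upper bound, not a description of what happens. A reader might infer a single central team that screens, holds the calls and knows the assignments; the article does not describe one. What remains is that the text does not separate the two functions either. Interventionists discuss cases in regular group meetings, the supervisor is a co-investigator, and the monthly investigator meetings review recruitment and enrolment. The block size itself is stated in the article, so it is open to review whatever the full protocol says about access.

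A reader might also infer a second fault, in the order of events: that couples are randomised before they schedule a session, that those who never schedule dilute the effect, and that the choice of interventionist could depend on arm. The documents do not support this.
- The article says "Couples are notified of their intervention assignment after scheduling their first session with the study interventionist". That fixes when couples are told, but does not expressly place assignment before scheduling.
- Because couples schedule without knowing their arm, their failure to schedule cannot be a reaction to it. This is a protective feature.
- It also says "Enrollment is determined at randomization, after both partners complete the baseline assessment". Counting every randomised couple is correct intention-to-treat practice.
- The article gives no rate of never scheduling, and no sign that interventionists are matched by arm; all are certified in both conditions.

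**Conclusion.** The point holds as a cheap improvement, not as a demonstrated bias. The plan fixes one small block size, publishes it during recruitment, and uses it where delivery staff are unmasked, outcomes are self-reported and a staff-run call precedes assignment. Up to 33% of assignments (about 32 of 100 dyads) are certain, and 71% can be guessed, for an observer who knows all earlier assignments in the stratum.

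These figures rest on that assumption about the observer; the article neither confirms nor excludes such a person. The arithmetic depends only on the stated 1:1 blocks of 4, and the allowance for unfinished blocks is insensitive to the stratum mix. The gain from the alternative lies in removing certainty (33% to about 9%). The gain in best-guess accuracy is small (71% to 68%). No conclusion follows about the order of scheduling, couples who never start, or dilution of the effect.

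**What to change.** For the couples still to be randomised:

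1. Generate a new REDCap list with permuted blocks whose size varies at random (for example 4, 6 and 8), within the same four strata. Do not disclose the sizes to enrolling or delivery staff, and do not publish them until recruitment closes.
2. Keep earlier assignments by stratum from the staff who enrol couples and hold orientation calls, and add a sentence to the protocol saying so. If such a rule already exists, state it.

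The cost is a regenerated list and one sentence of protocol text. It needs no extra participants or staff and no change to the strata or the analysis model. The downside is slightly looser balance between arms in small strata, where a larger last block is more likely to stay unfinished.

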### Interventions

#### Intervention overview

Participants in both conditions receive a manualized virtual psychosocial intervention, either OC or SS. The OC intervention includes 5 weekly sessions, and the SS intervention (comparison) includes 4 weekly sessions. Both interventions are delivered by a trained interventionist following a standard intervention protocol and integrating participant handouts with educational material and skill-building exercises. Each session is approximately 90 min. All sessions are audio-recorded. There are no restrictions on receipt of concomitant care participants may receive while enrolled in the study.

